## Abstract

**Background:**

Osteoporosis is a skeletal disease associated with high morbidity, mortality and increased economic costs. Early prevention during adolescence appears to be one of the most beneficial practices. Exercise is an effective approach for developing bone mass during puberty, but some sports may have a positive or negative impact on bone mass accrual. Plyometric jump training has been suggested as a type of exercise that can augment bone, but its effects on adolescent bone mass have not been rigorously assessed. The aims of the PRO-BONE study are to: 1) longitudinally assess bone health and its metabolism in adolescents engaged in osteogenic (football), non-osteogenic (cycling and swimming) sports and in a control group, and 2) examine the effect of a 9 month plyometric jump training programme on bone related outcomes in the sport groups.

**Methods/Design:**

This study will recruit 105 males aged 12–14 years who have participated in sport specific training for at least 3 hours per week during the last 3 years in the following sports groups: football (n = 30), cycling (n = 30) and swimming (n = 30). An age-matched control group (n = 15) that does not engage in these sports more than 3 hours per week will also be recruited. Participants will be measured on 5 occasions: 1) at baseline; 2) after 12 months of sport specific training where each sport group will be randomly allocated into two sub-groups: intervention group (sport + plyometric jump training) and sport group (sport only); 3) exactly after the 9 months of intervention; 4) 6 months following the intervention; 5) 12 months following the intervention. Body composition (dual energy X-ray absorptiometry, air displacement plethysmography and bioelectrical impedance), bone stiffness index (ultrasounds), physical activity (accelerometers), diet (24 h recall questionnaire), pubertal maturation (Tanner stage), physical fitness (cardiorespiratory and muscular), bone turnover markers and vitamin D will be measured at each visit.

**Discussion:**

The PRO-BONE study is designed to investigate the impact of osteogenic and non-osteogenic sports on bone development in adolescent males during puberty, and how a plyometric jump training programme is associated with body composition parameters.

## Background

Osteoporosis is a common skeletal disease associated with high morbidity and mortality [1]. Approximately 2.7 million European men and women suffer an osteoporotic fracture every year [2]. The economic burden of osteoporosis in Europe is higher than most types of cancer (except lung cancer), or chronic cardiorespiratory diseases [2,3] and represents a direct annual cost of ~ €31.7 billion to health care and social services [1]. In order to improve the outcome for osteoporosis, primary prevention remains the most important policy action in public health. Although contested [4], it is generally accepted that acquiring a high bone mass during childhood and adolescence is a key determinant of adult skeletal health [5-7]. Approximately 60% of osteoporotic cases in adult life are related to low bone mineral content (BMC) in adolescence with up to 50% of total body (TB) bone mass achieved during this period of life [8,9]. Peak bone mass attainment typically occurs between the second and third decade of life, with 80-90% acquired by late adolescence, although this is skeletal site dependent [6,10]. Although bone mass is ~ 60-80% genetically determined [11], there are other factors strongly related with bone mass development. Environmental and lifestyle factors such as physical activity (PA) [12] and nutrition, i.e. calcium intake [13] and vitamin D [14], are known to have important osteogenic effects and have been the key focus in several interventions.

### Exercise as a tool to improve bone health

Exercise has been proposed as a key factor for developing healthy bones in childhood and adolescence [15,16], mainly when high-impact and weight-bearing PA occurs [15] above a certain intensity and duration [15,17,18]. Longitudinal studies have shown that habitual PA is positively associated with bone health in children and adolescents because of its impact on bone development [19,20]. The long-term positive effects of PA during adolescence remain into young adulthood with active males aged 24.2 years having 8 and 10% higher BMC at TB and femoral neck (FN) respectively compared to non-active peers, even when adjusted for maturation and size [21]. Research conducted on former professional football players showed that exercise is not only an important factor in the accretion of, but also in the maintenance, of bone mineral density (BMD) [22]. It has been shown that moderate and readily accessible weight-bearing exercise before puberty may increase femoral volumetric BMC, by increasing cortical thickness, and therefore bone strength [23]. In addition, bone development is dependent on the impact of mechanical load and processes that trigger bone modelling and remodelling [24], and possibly on structural adaptations related with trabecular microarchitecture [25].

### Sport participation and bone health

It has been shown that sport participation is crucial for healthy bone development, however not all sports have a positive influence on the skeletal mass. According to their characteristics, sports can be described as osteogenic (weight-bearing exercise) and non-osteogenic (non weight-bearing exercise). Apart from numerous health benefits [26], football is considered as an osteogenic sport both in childhood and adolescence as bone mass is augmented [27-30]. In contrast, sports such as cycling [31-40] or swimming [41-46] are associated with no change or a reduction in bone mass when compared to controls. This could be a barrier for obtaining a high peak bone mass which may compromise future bone health [40,41,46,47].

### Plyometric exercise intervention to increase bone health

To achieve the benefits of exercise and gain acceptance, PA models must be effective, simple to administer, feasible, inexpensive, short in duration and possible to perform at any location (i.e. at home, at the sports centre). Plyometric jump training (PJT) may be a judicious choice and experimental studies using animal models have repeatedly shown that short, discrete bouts of exercise interspersed with rest periods is more effective than a single longer bout of exercise for improving bone mass and strength [48].

Research in early puberty has shown that a novel and easily implemented 8-month PJT (Bounce at the Bell; ~3 min/day) enhanced bone mass at the weight bearing proximal femur [49]. Mackelvie et al. showed that a 7-month jumping intervention (10 min, 3 times/week) was associated with more bone at the FN and lumbar spine (LS) in early pubertal girls [50], and these results were maintained after 2 years [51]. In addition, prepubertal Asian and Caucasian boys of average or low body mass index (BMI) augmented bone mineral accrual at several regions after a 7-month jumping intervention (10 min, 3 times/week). However, there are a lack of studies analysing the effect of PJT in the adolescent population, which is crucial as adolescence is the period associated with the greatest increments in BMC and BMD [52]. In addition, this has not been studied in adolescents engaged in different sports (osteogenic vs. non osteogenic), which is important to examine if peak bone mass during adolescence may be maximized and therefore reduce the risk for developing osteoporosis in adulthood.

### Bone turnover markers and vitamin D

Bone development depends on its metabolic activity, which includes bone formation, resorption and, as a consequence bone turnover [53]. The relationship of PA and sport participation with bone metabolism markers has been shown previously in adolescents [54,55]. An increase in the concentrations of bone formation and resorption markers can be observed in non-osteogenic sports, such as swimming, but a comparison between osteogenic and non-osteogenic sports has not been investigated previously [56].

The role of vitamin D in bone metabolism is important due to contribution of vitamin D in calcium homeostasis and bone mineralization processes during growth. Evidence shows that adequate vitamin D levels are necessary to acquire bone mass and interact with exercise to enhance bone growth [57,58]. The magnitude of the benefits in boys and girls differ at sites of the skeleton and may depend on the baseline levels of vitamin D and on previous loading experience [59]. A positive interaction between PA and vitamin D on BMD in adolescents has been described [60,61] however the association between vitamin D with osteogenic and non-osteogenic sports has not been justified.

### Objectives

The objectives of the PRO-BONE study are: 1) to longitudinally assess, over 3 years, bone health and its metabolism in adolescents engaged in osteogenic (football) and non-osteogenic (cycling and swimming) sports, and 2) after 12 months of sport participation to examine whether a short and inexpensive 9 months PJT intervention programme is positively associated with bone-related variables and its metabolism in adolescent footballers, cyclists and swimmers.

The secondary aim of the study is to examine whether the PJT programme stimulus is enough to counteract the expected negative consequences of these non-osteogenic sports in bone health and to follow-up the bone-related variables and its metabolism over 12 months after the PJT programme.

## Methods/Design

### Study design

PRO-BONE is a longitudinal design and involves four cohorts of males aged 12–14 years at the beginning of the study. These four cohorts consist of footballers, cyclists, swimmers and controls that will be followed over a period of 33 months. The timeline of the PRO-BONE study can be seen in Figure 1.

**Figure 1 Fig1:**
[figure not shown]
PRO-BONE timeline. FOO: Football players; CYC: Cyclists; SWI: Swimmers; PJT: Plyometric Jump Training.

### Sample size

The sample size has been calculated according to the primary interest variable, TB BMD (of cyclists (aged 15.5 years) [39] in order to achieve 90% of statistical power to detect differences in the contrast of the null hypothesis H0: μ1 = μ2 through bilateral student t, difference between two dependent means (matched pairs). Taking into account a significance level of 5% and assuming that the mean of the reference group 1.133 units (SD = 0.127) and the mean of the experimental group is 1.002 units (SD = 0.093), it will be necessary to include 9 participants in the reference group and 9 participants in the experimental group, totalling 18 participants. It is known that the number of participants to recruit depends also on potential withdrawals [or could use drop-outs]: n’ = n/(1-p), so that if the withdrawals were 40% the number of participants to be recruited would be n’ = 9/(1–0.4) = 15 in each group (e.g. 15 INT cyclists + 15 CON cyclists = 30 cyclists). Therefore, cyclists (n = 30), footballers (n = 30), swimmers (n = 30) and controls (n = 15) will be recruited, yielding a total N = 105.

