PRO-BONE will employ different and well known technological devices and methods such as DXA, BodPod, imaging bone ultrasonometer and triaxial accelerometers among others. In addition, the PJT will include a progression in intensity with ankle weights to maximize the potential to augment bone. PRO-BONE is timely as there is a lack of studies analysing the effects of PJT on bone health during the crucial this period of life. It represents a golden opportunity to measure how a simple, feasible and inexpensive PJT is associated with bone health in adolescents engaged in different sports. It will also show if the effect of this intervention differs between sports, expecting a greater effect in cyclists and swimmers than footballers. In addition, PRO-BONE will allow us to compare within each group and investigate changes in body composition in groups doing the PJT plus training vs groups only training. Finally, PRO-BONE will examine whether PJT has any additional effect on footballers. Football is considered one of the most osteogenic sports, but this type of intervention has not yet been studied.

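### The sample size rests on a matched-pairs t test, but the jump-training comparison is between two unmatched groups; an ANCOVA on the visit-2 scan fits the design

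*Protocol article*

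**What the plan says.** The Sample size section takes total-body BMD as its variable: "The sample size has been calculated according to the primary interest variable, TB BMD (of cyclists (aged 15.5 years"). It aims "in order to achieve 90% of statistical power to detect differences" at a two-sided 5% level in the "contrast of the null hypothesis H0: μ1 = μ2 through bilateral student t", and the same sentence goes on to describe that test as "through bilateral student t, difference between two dependent means (matched pairs"). The planning values are "the mean of the reference group 1.133 units (SD = 0.127") against 1.002 (SD 0.093) in the experimental group. The result is 9 per group, raised to 15 for 40% withdrawals. The section's example is 15 intervention plus 15 comparison cyclists, and the same number is applied to footballers and swimmers.

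The Abstract (Methods/Design) places the allocation at the second visit: "after 12 months of sport specific training where each sport group will be randomly allocated into two sub-groups". The Jumping intervention section confirms that randomisation is done separately in each sport. According to the Abstract, DXA and Tanner stage are measured at every visit.

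The Discussion says the study will "compare within each group and investigate changes in body composition in groups doing the PJT plus training vs groups only training". It also expects a larger effect in cyclists and swimmers than in footballers.

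**The concern.** A paired t test needs each observation in one arm to be linked to one in the other. Boys are divided at random within a sport and nothing links them in pairs, so the named test does not describe the comparison that objective 2 needs.

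Two things are at stake. First, the paired formula takes credit for a correlation that two unmatched arms do not have, so 9 per group is too few for the stated power. Second, the design does contain a usable correlation, between a boy's own scans at visit 2 and visit 3, as well as a known stratum (sport). The test on which the sample size rests uses neither. With about 9 completers per arm passing through puberty, chance imbalance in pre-intervention bone mass can weigh heavily on an unadjusted comparison.

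**Working it through.** **Inputs (Sample size section).** Means 1.133 and 1.002, difference 0.131; SDs 0.127 and 0.093; two-sided 5%; target power 90%; 9 completers per arm. The document gives no correlation, so every ρ and r below is an assumption. Power is from the noncentral t distribution.

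**1. The plan's own figure, as matched pairs.**

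SD of the difference = √(0.127² + 0.093² − 2ρ·0.127·0.093) = √(0.024778 − 0.023622ρ).

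- ρ = 0: SD 0.157, 18 pairs needed
- ρ = 0.5: SD 0.114, 11 pairs
- ρ = 0.6: SD 0.103, 9 pairs

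Exactly 9 pairs result only for ρ of about 0.58 to 0.64. The stated inputs alone do not give 9. The withdrawal step does reproduce: 9/(1 − 0.4) = 15.

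**2. The comparison actually made, two independent arms.**

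Pooled SD = √((0.127² + 0.093²)/2) = 0.1113. Standardised difference = 0.131/0.1113 = 1.18.

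- At 9 per arm: SE = 0.1113·√(2/9) = 0.0525; noncentrality 0.131/0.0525 = 2.50 on 16 df; power 65%.
- At 15 per arm (no withdrawals): power 87.5%.
- For 90%: 17 per arm.

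**3. With adjustment for the visit-2 value, 9 per arm in one sport.**

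ANCOVA residual SD = 0.1113·√(1 − r²), 15 df. For comparison, a change score from visit 2 has SD = 0.1113·√(2(1 − r)), 16 df.

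| assumed r | ANCOVA SD factor | ANCOVA power | change-score SD factor | change-score power |
|---|---|---|---|---|
| 0.5 | 0.866 | 77% | 1.000 | 65% |
| 0.7 | 0.714 | 90% | 0.775 | 86% |
| 0.8 | 0.600 | 97% | 0.632 | 96% |
| 0.9 | 0.436 | >99% | 0.447 | >99% |

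ANCOVA reaches 90% only from r of about 0.70. Its advantage over a change score is clear at r = 0.5 and small from 0.8 upwards.

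**4. Combining the three sports (27 against 27).**

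SE before adjustment = 0.1113·√(2/27) = 0.0303, against 0.0525 in one sport. With the ANCOVA, 54 − 5 = 49 df, and the average effect is the full 0.131, two thirds of it or one third of it:

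| effect of 0.131 present in | combined, r = 0 | combined, r = 0.7 |
|---|---|---|
| all three sports | 99% | >99% |
| cyclists and swimmers only | 81% | 98% |
| one sport only | 29% | 51% |

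The ANCOVA in one responding sport alone has 65% (r = 0) or 90% (r = 0.7). Combining helps in the first two patterns and loses in the third.

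**The case against.** The strongest objection is that the test appears only in the Sample size section. The article has no analysis section, and a covariate list or model is commonly left to an analysis plan, which is not shown. This stands in part: the absence of an adjusted model from the article is not a defect in itself. But the article does name a test, the test does not match the randomised comparison, and the sample size depends on it. That is something fixed badly, not something left out.

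A reader might infer that the final analysis will be an unadjusted two-sample t test that ignores the visit-2 scan. The documents do not support that. The named test is paired, and the Discussion speaks of comparing changes, which may imply a change score from a pre-intervention measurement. Against that comparison the gain from ANCOVA is smaller, as the table shows.

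A reader might also infer that pooling the sports recovers precision at no cost. No new data are needed, but the question changes. The article sizes each sport separately, has a secondary aim about the non-osteogenic sports, and asks separately about footballers. A combined effect averages over sports that are expected to differ, and it loses power if only one responds.

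**Conclusion.** The point holds for the mismatch: a matched-pairs test is used to size a comparison of unmatched randomised arms. On the stated inputs, 9 completers per arm give about 65% power, not 90%. Adjusting for the visit-2 scan is feasible and would raise this to about 77%, 90% or 97% at r = 0.5, 0.7 or 0.8. The size of the gain depends wholly on r, which the document does not give.

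The calculations take 0.131 as it stands, and neither the test nor the fix makes that figure more secure. It is a gap between two group means taken from cyclists aged 15.5 years, with the experimental mean the lower one. At half that difference (0.0655), power at 9 per arm is 22% unadjusted and 37% with ANCOVA at r = 0.7.

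The change should be made, but the material does not show that the final analysis will be wrong.

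**What to change.** In the Sample size section, or wherever the analysis is defined:

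- Drop the matched-pairs t test.
- State the jump-training comparison as an ANCOVA of post-intervention total-body BMD on arm, visit-2 total-body BMD and sport (the randomisation stratum). Visit-2 height and Tanner stage are optional further covariates.
- Estimate the sport-specific effects from the same model through an arm-by-sport term.
- State the assumed visit-2 to visit-3 correlation with its source, and recompute the number per arm from it. Without adjustment the stated inputs need 17 completers per arm.
- Report a combined estimate alongside the sport-specific ones if wanted. Whether it is the primary test is for the sponsor to decide and to fix in advance.

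The analysis change costs wording only, because visit-2 BMD, height and Tanner stage are already in the measurement schedule. If the correlation that can be justified is below about 0.70, 9 completers per arm will not give 90% power within a sport. The claimed power or the recruitment target would then have to change.

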### Jumping intervention

Following 12 months of sport specific training, the randomisation process will start in each sport group and participants will be divided into two sub-groups to perform a PJT programme as follows: 1) intervention programme groups, (sport + PJT) and 2) sport groups (sport only). It has been shown that 7 to 9 month PJT programmes can effectively improve BMC and/or BMD at different skeletal sites in children and adolescents and to maintain the benefits for 3 years after the intervention [52,87]. Therefore, a progressive PJT (~10 min/day) will be performed by intervention groups 3 to 4 times/week (depending on progression) as shown in Table 1. Before the intervention, trained staff will ensure that participants fully understand and correctly execute the different jumps and a research assistant will meet with the participants to observe, demonstrate and review the jumps. Participants will be instructed to perform a number of countermovement jumps (CMJ) and squat jumps (SJ) on a hard surface. Jumps will be performed before and after school and before going to bed. The CMJ will be performed by bending the knees prior to the jump. The CMJ activates the stretch-shortening cycle in the muscles, resulting in greater power production in the legs compared to a SJ. For the SJ participants will squat down until the knees are bent at 90 degrees, then they will immediately jump vertically as high as possible, landing back on the ground on both feet simultaneously. For this technique, the participant starts from a stationary semi-squatting position, or pauses at the lower level of the squat before jumping upwards. This removes the factor of the stretch-shortening cycle. The reliability and validity of the CMJ and SJ has been previously reported [88,89].

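### The sample size rests on a matched-pairs t test, but the intervention and sport-only arms are independent randomised groups, so the stated 90% power is unsupported for that contrast (about 65% unadjusted with 9 completers per arm)

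*Protocol article*

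**What the plan says.** The Sample size section names total body BMD as the variable that drives the calculation: "The sample size has been calculated according to the primary interest variable, TB BMD". The target is set "in order to achieve 90% of statistical power to detect differences" at a two-sided 5% level, and the test is specified as "through bilateral student t, difference between two dependent means (matched pairs").

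The inputs are a mean and SD for each of two groups: "the mean of the reference group 1.133 units (SD = 0.127") and "the mean of the experimental group is 1.002 units (SD = 0.093"). The result is that "it will be necessary to include 9 participants in the reference group and 9 participants in the experimental group, totalling 18 participants". Allowing for 40% withdrawal, the section raises 9 to 15 per group and illustrates this with 15 intervention and 15 comparison cyclists, 30 in all. The same number is carried to footballers and swimmers, and 15 controls bring the total to 105.

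The Jumping intervention section says how the two groups within a sport arise: after 12 months "the randomisation process will start in each sport group and participants will be divided into two sub-groups", one doing the sport plus jump training and the other the sport only. The Abstract (Methods/Design) describes the same random allocation.

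**The concern.** A matched-pairs test applies when each observation in one group has a partner in the other. Here the two groups are separate boys allocated at random, and the article describes no partnering of a boy in one arm with a boy in the other. The calculation also mixes two designs. It counts participants as two separate groups (9 + 9 = 18) but takes the number from a paired test, for which 9 would mean 9 pairs sharing a within-pair correlation. That correlation is not stated, so the 9 cannot be checked even on its own terms.

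This is the only justification the article gives for 30 boys per sport and a total of 105. If power for the jump-training contrast within a sport is nearer 65% than 90%, the chance of missing the assumed difference is about 35% rather than 10%. A reader who relied on the stated power would give a non-significant result in one sport more weight than it deserves.

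**Working it through.** **Inputs, all from the Sample size section.** Means 1.133 and 1.002; SDs 0.127 and 0.093; two-sided 5%; target power 90%; 9 completers per group; 40% withdrawal. Not stated: any correlation.

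**Step 1: reproduce the 9.** For a paired t test, SD of the difference = √(s₁² + s₂² − 2·r·s₁·s₂), with noncentrality = 0.131·√n / SD of the difference and n − 1 degrees of freedom. Since r is not given, I varied it.

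| assumed r | SD of difference | power with 9 pairs | pairs needed for 90% |
|---|---|---|---|
| 0 | 0.1574 | 59.2% | 18 |
| 0.5 | 0.1139 | 85.5% | 11 |
| 0.55 | 0.1086 | 88.5% | 10 |
| 0.6 | 0.1030 | 91.5% | 9 |
| 0.7 | 0.0908 | 96.5% | 8 |

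Exactly 9 pairs is the answer only for r between about 0.575 and 0.645. The stated figure can thus be reproduced, but only by supplying a correlation that the article does not give. The withdrawal step is correct: 9/(1 − 0.4) = 15.

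**Step 2: the same inputs with independent groups.**
- Pooled SD = √((0.127² + 0.093²)/2) = 0.1113.
- Standardised difference = 0.131/0.1113 = 1.177.
- Noncentrality = 0.131/(0.1113·√(2/n)), with 2n − 2 degrees of freedom.

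| completers per arm | noncentrality | power |
|---|---|---|
| 9 | 2.497 | 65.0% |
| 15 | 3.223 | 87.5% |
| 16 | 3.329 | 89.6% |
| 17 | 3.431 | 91.4% |

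So 17 completers per arm are needed for 90%. Even all 15 recruited boys per arm, with no losses, fall just short.

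**Step 3: sensitivity at 9 per arm.** Welch's test gives about 64%, simulation of the pooled test 65.0%, and the normal approximation 70.4%. Using only the larger SD gives 54% and only the smaller 80%. A one-sided test gives 77%. None reaches 90%.

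**Step 4: baseline adjustment.** If r is instead the correlation between baseline and follow-up BMD, ANCOVA reduces the residual SD to 0.1113·√(1 − r²). With 9 per arm and 15 degrees of freedom:

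| assumed r | residual SD | power |
|---|---|---|
| 0.5 | 0.0964 | 76.9% |
| 0.6 | 0.0890 | 83.0% |
| 0.7 | 0.0795 | 90.4% |

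**Step 5: sport against controls at baseline.** With 30 against 15 boys, pooled SD 0.1113 and 43 degrees of freedom, noncentrality is 3.722 and power is 95.3%. With Welch's test, SD 0.127 for the 15 and 0.093 for the 30, it is 92.3%.

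**The case against.** The best defence is that the study is longitudinal with five visits. An analysis that uses each boy's earlier measurements would be more efficient than a cross-sectional t test, and the analysis model may stand in a document not shown. This stands in part. Step 4 shows that baseline adjustment could bring 9 per arm to about 90% if the correlation is near 0.7. It follows that 65% is the power of an unadjusted comparison, and a reader who took it as the power of the trial's eventual analysis would go further than the article allows. But the calculation as written contrasts two groups through their cross-sectional SDs and states neither an adjusted analysis nor a correlation. Nor can it be read as a before-and-after test: that would need one group of 9 rather than 9 + 9, and would not compare jump training with sport alone.

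Two stronger readings are tempting and should be resisted. One is that 90% fails for every comparison between different boys. Step 5 contradicts this: at baseline, before losses and before randomisation, a whole sport against controls exceeds 90% on the same inputs. The other is that the design contains no matching at all. The Abstract describes the control group as age-matched. That concerns the 15 controls, not the randomised arms, and no boy-to-boy pairing is described there either, so it does not justify a paired test.

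**Conclusion.** The point holds for the within-sport contrast of sport plus jump training against sport only. The test used for sizing does not fit two independently randomised groups, and the correlation it needs is missing. On the stated inputs, an unadjusted two-sided 5% comparison has about 65% power with 9 completers per arm and about 87.5% with 15, against the stated 90%; 17 completers per arm would be needed. These figures assume normal outcomes, the stated SDs and a true difference of 0.131, and they are conditional on no baseline adjustment. How the 9 was reached cannot be settled from the article: a correlation near 0.6 would give it, and so would 18 pairs at zero correlation misread as 18 boys. The conclusion depends on neither.

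**What to change.** Rewrite the power paragraph in the Sample size section in one of two ways.

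1. Replace the matched-pairs calculation with one for independent groups and state the power it gives for a difference of 0.131: about 65% with 9 against 9 completers and about 87% with 15 against 15.
2. Base the power on a baseline-adjusted (ANCOVA) comparison. State and justify the assumed baseline-to-follow-up correlation and show a range, such as 77%, 83% and 90% at 9 per arm for correlations of 0.5, 0.6 and 0.7. The correlation should come from data, not be chosen because it returns 90%.

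Either way, say which comparison the power refers to and remove the 90% claim tied to the paired test. The cost is one rewritten paragraph and a less favourable stated power. Correcting the statement needs no change in recruitment. Keeping 90% for an unadjusted comparison at 40% withdrawal would: 17/0.6 = 28.3, so 29 per arm and 58 per sport, against the planned 15 and 30.

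### The 90% power rests on a total-body BMD difference of 0.131 (11.6%) from a study of cyclists, never justified as a jump-training effect, yet it is applied to the randomised jump-training contrast in all three sports

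*Protocol article*

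**What the plan says.** All the planning inputs stand in the Sample size section. The endpoint and source are "TB BMD (of cyclists (aged 15.5 years) [39", that is, a cited study of cyclists. The calculation is made "in order to achieve 90% of statistical power" at a two-sided 5% level, "through bilateral student t, difference between two dependent means (matched pairs". The planning values are "mean of the reference group 1.133 units (SD = 0.127) and the mean of the experimental group is 1.002 units", the latter with SD 0.093. This gives 9 per group, raised to 15 per group for 40% withdrawals.

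The section then names the comparison that receives this number: "15 INT cyclists + 15 CON cyclists = 30 cyclists". Thirty cyclists split into INT and CON are the two randomised sub-groups of the Jumping intervention section: sport plus plyometric jump training (PJT), and sport only. The same 30 is set for footballers and for swimmers.

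Elsewhere, the section on sport participation and bone health cites a block of studies that includes this source for the statement that "sports such as cycling [31-40] or swimming [41-46] are associated with no change or a reduction in bone mass when compared to controls". The Objectives expect PJT to be positively associated with bone variables. The Discussion expects a greater PJT effect in cyclists and swimmers than in footballers.

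**The concern.** The number of boys per arm and the 90% power are attached to the randomised PJT question, but the difference behind them seems to answer another question: how far cyclists' bone density differs from that of a reference group. No section gives a PJT effect on total-body BMD or says that 0.131 is the expected or targeted gain from nine months of jumping.

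PJT is the only randomised comparison in the study, and the Discussion announces comparisons of PJT plus training with training alone within each group. If the true PJT effect is well below 11.6%, each of these comparisons has much less than 90% power. A reader who takes the stated power at face value could then read a non-significant result in one sport as evidence that jumping does not help.

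**Working it through.** **Inputs from the protocol (Sample size).** Reference mean 1.133, SD 0.127; experimental mean 1.002, SD 0.093; two-sided 5%; 90% power; 9 per group, 15 after withdrawals. The section gives the values in "units"; the DXA section reports BMD in g/cm².

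**Inputs assumed here.** Correlation r between baseline and follow-up BMD, and any PJT effect below 0.131. The protocol gives neither.

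**1. The planned difference.** 1.133 − 1.002 = 0.131; 0.131/1.133 = 11.6%. The lower mean is in the group called experimental. Pooled SD = √[(0.127² + 0.093²)/2] = 0.1113; standardised difference = 0.131/0.1113 = 1.18.

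**2. The plan's own figure.** For a paired t-test, the SD of differences is √(0.127² + 0.093² − 2ρ × 0.127 × 0.093), and the protocol states no within-pair correlation ρ. By the noncentral t distribution, 90% power needs 18 pairs at ρ = 0, 13 at 0.3, 11 at 0.5, and 9 for ρ of about 0.575 to 0.645. So 9 is attainable but cannot be derived from the stated inputs alone. The later steps reproduce: 9/(1 − 0.4) = 15, and 3 × 30 + 15 = 105.

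**3. What 9 to 15 per arm can detect.** The randomised sub-groups are independent, so I use a two-sample t-test (noncentral t, 2n − 2 degrees of freedom). The standardised difference detectable with 90% power is 1.629 at n = 9 and 1.226 at n = 15. Baseline adjustment reduces the SD to 0.1113 × √(1 − r²): 0.0485 at r = 0.9 and 0.0348 at r = 0.95. Taking off one more degree of freedom for the covariate changes the adjusted values by less than 0.001.

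| Analysis | 9 per arm | 15 per arm |
|---|---|---|
| Unadjusted | 0.181 (16%) | 0.137 (12%) |
| Adjusted, assumed r = 0.9 | 0.079 (7.0%) | 0.060 (5.3%) |
| Adjusted, assumed r = 0.95 | 0.057 (5.0%) | 0.043 (3.8%) |

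Percentages are of 1.133.

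**4. Power for a smaller effect, as illustration only.** Take an assumed PJT effect of 3%, which is 0.03 × 1.133 = 0.034 g/cm².

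| Analysis | 9 per arm | 15 per arm |
|---|---|---|
| Unadjusted | 9% | 13% |
| Adjusted, assumed r = 0.9 | 29% | 46% |
| Adjusted, assumed r = 0.95 | 49% | 73% |

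**The case against.** The test is two-sided, so the sign of the planned difference does not affect sample size or power. A reader might infer from the lower experimental mean that the calculation says nothing about PJT, or that the wrong direction invalidates it. Neither follows: the calculation would speak to a PJT effect of 0.131 in either direction. The secondary aim of counteracting the harm of non-osteogenic sports even offers a possible rationale, with PJT fully reversing a cyclist deficit. This part of the objection stands. But the protocol does not make that argument for its sample size, and it would not carry over to footballers, for whom the protocol describes a bone gain and expects a smaller PJT effect, yet sets the same number.

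The source is not at hand, and neither section says outright that 1.133 and 1.002 are control and cyclist means. This stands too: the cycling-versus-control reading is an inference for the sponsor to confirm.

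A reader might also call 11.6% implausible because the Background cites active men as "having 8 and 10% higher BMC at TB and femoral neck (FN) respectively compared to non-active peers". The comparison is not like for like. It concerns bone mineral content in men aged 24.2 years, adjusted for maturation and size, whereas the planning values are bone mineral density in cyclists aged 15.5 years with no adjustment stated. It does not show that 11.6% is out of reach.

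Finally, the shortfall depends on assumed effects and correlations, and 9 per arm is the full-withdrawal case. With adjustment at an assumed r = 0.7, 9 per arm detects 0.130 with 90% power, so 0.131 itself could be covered. Hence the ranges above. They soften the shortfall but do not turn 0.131 into a justified PJT effect. The use of a paired formula for independent arms is a separate matter and is not needed for this point.

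**Conclusion.** The point holds in this form: the protocol assigns 90% power to the randomised PJT comparison on the strength of a difference of 0.131 g/cm² (11.6%) that it takes from a study of cyclists and nowhere justifies as a PJT effect. The claim does not extend to smaller PJT effects. Within one sport, with 9 to 15 boys per arm, the difference detectable with 90% power runs from 16% to 12% unadjusted and from 5.0% to 3.8% at the most favourable correlation shown.

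These figures rest on the protocol's two SDs, independent arms and a two-sided 5% test; the adjusted ones also rest on the assumed correlations. The 3% effect is an illustration, not a prediction. The documents do not show that a PJT effect of 11.6% is impossible, nor how results will be reported.

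**What to change.** In the Sample size section:

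- State which two groups of the cited study the means 1.133 and 1.002 describe, after checking the source, and so what 0.131 represents.
- Remove the 90% power claim for the PJT objective.
- In its place, give the smallest PJT difference detectable with 90% power at the fixed 9 to 15 per arm within a sport, with the SD and the baseline correlation assumed, for example as in the first table above.
- Label any PJT effect size used for illustration as an assumption, and show power at both 9 and 15 per arm.

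The cost is a rewording and a less favourable stated power. Recruitment, arms and measurements stay as they are, and no additional participants are needed.
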